### Data collection

From each participant, we will collect data linked to each of the research questions and objectives. The variables are listed in Table 1 including the instruments used and the ways to collect these data. These variables will be collected for all participants at baseline, one year and two years after inclusion by trained research staff who will interview participants guided by written questionnaires, and who will perform physical examination and collect blood samples.

**Table 1 T1:** List of variables, measuring instruments and data sources

	**Variable**	**Instrument**	**Data collection method**
**Health outcome indicators**			
	HbA1C	DCA Vantage (Siemens)	Blood samples taken by trained field researchers, analysed by laboratory staff at location. Results on a patient record form
	Blood pressure	Electronic sphygmomanometer from certified manufacturer, study Standard Operating Procedure (SOP)	By trained field researchers, on patient record form
	BMI	Height and weight measured by research staff, study SOP	By trained field researchers, on patient record form
	Waist/Hip ratio	Conventional measuring tape according to study-SOP	By trained field researchers, on patient record form
	Diabetic foot lesions (nr)	Number of active wounds on both feet, detected through systematic examination by trained research staff	By trained field researchers, on patient record form
**Access to care indicators**			
	Attendance of DSME and medical care	Self-report over 12-month period: number of educator-contacts (check DSME patient records), visits to medical doctor, kidney-function test	Interviews with paper questionnaire, by researchers (Q28, 30, 31)
	Total medical expenditure	Self-report	Interviews with paper questionnaire, by researchers (Q32 a+b)
	Total time for h care visits	Self-report	Interviews with paper questionnaire, by researchers ( Q32c+d)
**Quality of support indicators**			
	Perceived Quality of Care DSME	PACIC score (Glasgow et al. [33])	Interviews with paper questionnaire, by researchers (Q33a-t)
	DSME needs and services	6-elements questionnaire, inspired by Diabetes Care Profile [34]	Interviews with paper questionnaire, by researchers (Q34+35)
	Enablement through DSME	Patient enablement score [35]	Interviews with paper questionnaire, by researchers (Q36)
**Empowerment indicators**			
	Level of knowledge on diabetes (care)	Diabetes Knowledge Score, adapted from Brief Diabetes Knowledge Test & the Diabetes Knowledge Questionnaire ([36,37])	Interviews with paper questionnaire, by researchers (Q13)
	Attitude towards diabetes	Attitude scale Diabetes Care Profile [34]	Interviews with paper questionnaire, by researchers (Q14)
	Feeling of control	Control scale from Diabetes Care Profile [34]	Interviews with paper questionnaire, by researchers (Q15a-d)
**Self-management behaviour**			
	Adherence to glucose monitoring & control	Self-report of last time self-monitoring, professional monitoring, medication taking	Interviews with paper questionnaire, by researchers (Q16-25)
	Adherence to exercise & diet	Self-report	Interviews with paper questionnaire, by researchers (Q38/37, 41)
**Process indicators**			
	Number of SMS sent (ProjIC) to participant	Database that is used to send out ProjIC	Assessment by the project manager
	Number and type (call or SMS) of PatIC to educators	Telephone provider records	Assessment by the project manager
	intervention cost at DSMS programme level	Extraction from data from project documents	Collected by country research team
**Context characteristics**			
Diabetes prevalence, phone penetration, literacy rate, DSME programme characteristics	extraction from data from project documents, country-related publications and other secondary data	Collected by country research team	
	Knowledge and professional habits of diabetes care providers	Provider Profile, Diabetes Management Practices and Brief Diabetes Knowledge & Practice Test (adapted from ([38])	Written self-administered questionnaire to health providers

The patient questionnaire (Additional file 1) includes several scales that measure dimensions of chronic care: the ‘needs & services-scale’, ‘attitude scale’ and ‘control scale’ which are all subscales from the Diabetes Care Profile (DCP) [34]; the ‘patient enablement score’ [35]; and the Patient Assessment of Chronic Illness Care (‘PACIC Score’) [39]. These scales have been validated in heterogeneous populations in clinical and community settings in western countries [34,33]. The ‘patient enablement score’ has been validated in a low income country [40]. The questionnaire was developed for a study involving persons with diabetes in the Philippines. Results of that study are yet to be published. The questionnaires will be translated into local languages and pretested in all countries. We will also collect the following personal and diabetes (care) related variables: age, sex, education, diabetes history (year of diagnosis, hospital admissions, treatment, hypertension) and physical access to care (distance to care providers). For the process analysis, we will assess the number of SMS sent to each participant in the intervention group and the number of phone calls / SMS that participants of both groups made to the educator.

For each country, we collect a number of contextual characteristics from primary and secondary sources. These are: prevalence of diabetes, mobile phone penetration, literacy rate, details about the existing DSME programme (number of patients per educator, components of DSME strategies, frequency of contact between patients and educator, etc.), presence of patient organisations and knowledge and professional habits of diabetes care providers (through self-administered questionnaire sent to diabetes care providers in the environment).

Data will be electronically entered and cleaned through Epi-Info, using a double-entry procedure.

The main secondary variables of interest are: difference in change of mean blood pressure, mean BMI and mean waist/hip ratio. Secondary variables will be assessed using similar logistic regression or ANOVA/regression (for continuous data) models. Outcome indicators will be plotted over time. Repeated measure models will be used to analyse longitudinal trends over time or to correct for missing data and hierarchical models will be used to assess the influence of educator characteristics on the effects.

Recruitment will be evaluated by assessing the number of individuals who are: part of the target population informed about the study and requested to participate; meeting the inclusion criteria; having signed the informed consent; and having been enrolled in one of the study arms. Loss-to-follow up will be measured by subtracting the number of individuals in each arm of the study returning for evaluation at determined moments of evaluation from the total number of participants at inclusion.

### Multi-country analysis

After the analysis of the effectiveness of the intervention in each country, we will perform a multi-country analysis. We will analyse if any statistically significant differences in the primary and secondary end-points can be detected between the three countries. We will use a realistic approach to look for factors explaining any identified differences between countries, explaining how the actual intervention led to the observed results and why the results differ (or not) between countries [41-43]. Project documents, project reports from the field sites and observation reports will be collected. In-depth interviews will be carried out with project managers and diabetes educators and focus group discussions with patients from both groups will be carried out. Triangulation of data will be done by comparing the results from these sources. The interview recordings will be transcribed verbatim and entered in N-Vivo. Qualitative data analysis will be carried out using the programme theory as the analytical framework [44,45].

### Cost-effectiveness analysis

In addition, we will conduct an incremental cost-effectiveness analysis (CEA) comparing the DSMS strategy in addition to the existing DSME strategy with the DSME strategy only. The evaluation will take the societal viewpoint taking into account both patient and programme costs. Costs incurred by patients consist of direct medical (e.g. cost for consultation, medication and the cost for urgent care and hospitalisation), direct non-medical (cost for using mobile phone for PatIC, travel cost, food cost, cost related to exercise) and indirect costs. Indirect costs include the value of time spent by participants visiting educators and other health care providers and the loss of productivity due to illness. Programme costs include the cost for development and management of the intervention and the cost for telecommunication. Information about patient direct and indirect costs will be collected by a trained field researcher with a patient questionnaire (see section on data collection). The value of time losses will be estimated from secondary sources taking the GDP of the three countries into account. The information on programme costs will be collected prospectively by keeping a detailed account of all expenditures at the programme level. Programme effectiveness will be expressed in terms of the percentage increase of people with diabetes with a controlled HbA1C level [46,47].

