### Study design

The study consists of three sub-studies with a similar design in three low-to-middle income countries, which will be independently implemented and analysed. The design is a two-arm Randomised Controlled Trial (RCT), in which a total of 480 adults with diabetes (type 2 or 1) participating in an existing DSME programme in each country, will be randomly allocated to either self-management education as provided by the existing programme (usual care)or to self-management education plus a mobile phone self-management support intervention. Participants in both arms complete assessments at baseline, one year and two years after inclusion.

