### Intervention

The content and process of DSMS is based upon the minimum DSME package and on elements of behaviour theory, aiming to influence the modifying factors of behaviour. DSMS messages can, for instance, increase knowledge about certain behaviours and their effects, they can create normative beliefs and social pressure and they can provide emotional support and increase the perception of control by people with diabetes. Messages for DSMS will follow the nine dimensions of DSME, but will be locally developed and validated through consultations with DSME staff and people with diabetes. The local validation pertains to the local meaning of health behaviours (for instance what is a healthy diet) but also to locally relevant modifying factors of behaviour (constraints for doing physical exercise). The participants allocated to the intervention group will receive a regular mobile phone. They will receive standardised and individualised Project-Initiated Communication (ProjIC) through Short Messaging Services (SMS), which implies the maximum length of messages being 160 characters. The software FrontLine is used to send SMS in an convenient way. Furthermore, people are encouraged to use the phone to contact other people including fellow patients, educators and providers to ask for advice or provide information when needed, for instance when they cannot come to an appointment. Depending on the arrangements with the national telephone providers, participants will be provided with a budget for calls and messages. This is termed Patient-Initiated Communication (PatIC).

To control for the potential effect of providing participants with a regular mobile phone, the participants allocated to the usual care group will also receive a mobile phone but will not receive ProjIC. They will however continue to receive assistance from their educators according to the DSME programme.

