The educators are not involved in the initiation of DSMS-related communication. However, all educators will be provided with a regular mobile phone so that they can be reached by patients. They will receive a modest monthly allowance to compensate them for the additional work and costs that they will have because of the intervention: receiving more calls/SMS from patients; taking necessary action upon these; and being involved in the data collection for physical examination and blood sampling. They will continue to provide DSME to their patients irrespective of their allocation to one of the trial arms.

The study project manager in each country is the central person in providing ProjIC to the people in the DSME+DSMS group. He/she will be provided with a smart phone with instructions and training on how to use it. He/she will enter patient-related data into a database that is developed and managed at national level and send out ProjIC to patients that belong to the DSME+DSMS group in the different participating centres/field sites. He will support and give feedback to educators when necessary and coordinate research data collection at site level.

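### The cost-effectiveness analysis names existing DSME only as comparator, but no arm receives it: controls also get a phone and phone-equipped educators with an allowance

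*Protocol article*

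**What the plan says.** The Cost-effectiveness analysis section sets the incremental comparison as "comparing the DSMS strategy in addition to the existing DSME strategy with the DSME strategy only". Study design agrees: participants are "randomly allocated to either self-management education as provided by the existing programme (usual care") or to the same education plus mobile phone support. The Discussion calls the controls the DSME-only group.

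The Intervention section describes what is delivered. DSMS has two parts: project-initiated communication (ProjIC), sent by SMS, and patient-initiated communication (PatIC), in which patients are encouraged to call or text educators and others, possibly with a call budget. In the control arm, "the participants allocated to the usual care group will also receive a mobile phone but will not receive ProjIC". The reason given is "To control for the potential effect of providing participants with a regular mobile phone". On the educators' side, "all educators will be provided with a regular mobile phone so that they can be reached by patients", and "They will receive a modest monthly allowance to compensate them for the additional work and costs" that the intervention brings. That work includes more calls from patients and help with examinations and blood sampling. Educators serve patients of both arms. Data collection provides for counting "the number of phone calls / SMS that participants of both groups made to the educator".

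On costs, the article lists developing and managing the intervention and telecommunication, and it plans a prospective record of all programme spending. It does not say to which arm handsets and educator allowances are charged. On effect: "Programme effectiveness will be expressed in terms of the percentage increase of people with diabetes with a controlled HbA1C level".

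**The concern.** The comparator named for the cost-effectiveness analysis is a programme without project phones and without phone-equipped educators on an allowance. No randomised group receives that programme. The Discussion's paragraph on contamination does not cover this, because it concerns contact between patients and not phone access supplied by design to both arms.

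The Discussion says that the results will inform decision-makers about implementation. A programme manager who reads a ratio labelled DSMS against DSME only would take it as the cost and yield of adding mobile phone support to an ordinary programme. The trial measures a narrower increment, and the label does not say so. How far the reported ratio departs from the labelled one, and in which direction, depends on a cost assignment that the article leaves open.

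**Working it through.** **Step 1: set the arms side by side** (Intervention and Data collection sections).

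| Element | Intervention arm | Control arm | Named comparator (DSME only) |
|---|---|---|---|
| DSME, upgraded to the minimum package | yes | yes | yes |
| Handset for the patient | yes | yes | no |
| Educator with phone and allowance | yes | yes | no |
| ProjIC messages | yes | no | no |
| Encouragement to call | yes | not stated | no |
| Call budget | depends on provider arrangements | not stated | no |

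The control column differs from the comparator column in at least two rows. Between the arms, ProjIC differs for certain; encouragement and call budget may differ.

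**Step 2: what follows for the ratio.** The article gives no cost and no cost-effectiveness figure, so there is nothing to reproduce. The inputs are:
- Package effect: 0.15, the planned difference in the Sample size calculation section, taken here as an improvement from 60% to 75%.
- M = 1: cost per participant of what only the intervention arm receives (assumed unit).
- S = 0.5 to 2: cost per participant of handsets and educator support common to both arms (assumed).
- f = 0 to 0.5: share of the package effect that comes from phone access, which controls also have (assumed).

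The formulas are:
- Ratio for the labelled comparison, package over ordinary DSME: (M + S) / 0.15.
- Ratio from the randomised contrast, shared costs cancelling: M / [0.15 × (1 − f)].
- Ratio if shared costs are all charged to DSMS: (M + S) / [0.15 × (1 − f)].

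| S | f | Labelled | Shared costs cancel | Shared costs charged to DSMS |
|---|---|---|---|---|
| 0.5 | 0 | 10.0 | 6.7 (0.67×) | 10.0 (1.0×) |
| 0.5 | 0.5 | 10.0 | 13.3 (1.33×) | 20.0 (2.0×) |
| 1 | 0.2 | 13.3 | 8.3 (0.62×) | 16.7 (1.25×) |
| 2 | 0 | 20.0 | 6.7 (0.33×) | 20.0 (1.0×) |
| 2 | 0.5 | 20.0 | 13.3 (0.67×) | 40.0 (2.0×) |

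If shared costs cancel, the reported ratio is 1 / [(1 + S)(1 − f)] times the labelled one, which is 0.33 to 1.33 over these ranges. If they are charged to DSMS, it is 1 / (1 − f) times, which is 1.0 to 2.0. Neither rule recovers the labelled ratio in general. The first can err in either direction.

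**Step 3: the effect measure.** From 60% to 75% is 15 percentage points, or (0.75 − 0.60) / 0.60 = 25% in relative terms. The two readings differ by 25 / 15 = 1.67. The article uses 15% for the between-arm difference in its sample size section, so the absolute reading is the likely one. This is a matter of wording.

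**The case against.** The strongest defence is that DSME only is shorthand. The Discussion uses DSME-only group for the control arm, and the Intervention section says openly what that arm receives and why. Giving controls a phone isolates the messages from the handset, which is a sound design choice. Cost-assignment rules are commonly left to a fuller protocol or analysis plan. This defence stands as far as it goes: the randomised comparison and the primary test are untouched, and the absence of an allocation rule is not itself a fault. It does not remove the contradiction, because the article fixes the comparator of an economic analysis as a strategy, and that strategy was not randomised.

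A reader might go further and infer two things that the document does not support.

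- *That the contrast is messages alone.* Encouragement to call and a possible call budget are described for the intervention arm. For controls only ProjIC is expressly withheld, and the text is silent on the other two. They may be part of the contrast.
- *That the incremental cost is understated.* That would need shared costs to be netted out or omitted. All programme spending is to be recorded, the cost list need not be exhaustive, and the allowance is attributed to the intervention, so charging it to DSMS is a natural reading. The incremental cost would then not be understated, and the problem would become a package cost paired with a narrower effect.

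Part of the allowance also pays for research data collection and does not belong to DSMS. Nor does the article say that a scaled-up programme would have to supply handsets.

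**Conclusion.** The point holds as a mismatch between the stated comparator and the arms as delivered. The trial can estimate mainly the effect of ProjIC, with any arm-specific encouragement and call budget, on top of DSME with phones and phone-equipped educators. It cannot directly estimate the effect or the cost-effectiveness ratio of the whole DSMS package over ordinary DSME.

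The direction of any error in the ratio is indeterminate. The ranges of 0.33 to 1.33 and 1.0 to 2.0 illustrate this and rest wholly on the assumed S, f and M; they are not estimates for this trial. If phone access contributes nothing to HbA1C control (f = 0), charging shared costs to DSMS gives the labelled ratio exactly.

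The consequence falls on what the cost-effectiveness result, part of the secondary aim, may claim, and on how the primary result is described. Internal validity is not in question.

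**What to change.** 1. In Objectives, Study design and Cost-effectiveness analysis, name the contrast as randomised: ProjIC, with any encouragement and call budget specific to the intervention arm, added to DSME in which patients and educators have phones.
2. State whether controls receive the call budget.
3. Limit the base-case ratio to that contrast. Costs common to both arms cancel, and the effect is the between-arm difference in percentage points.
4. Add one scenario that charges the non-research part of handset, airtime and educator costs to DSMS. Label it as pairing a package cost with an effect that excludes whatever phone access contributes.

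The cost is some rewording and one extra scenario from spending records that are already planned, with an explicit assumption for splitting the allowance between research and support work. Design and patient data collection do not change. The downside is a narrower claim and a less favourable ratio in the scenario.

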## Discussion

The central hypothesis that will be tested in this study is that a mobile phone DSMS intervention on top of an existing DSME programme will improve clinical outcomes for people with diabetes, measured by their HbA1C level. The wide range of secondary variables will yield information on intermediary outcomes and on other outcomes which are also very relevant for the organisation of support.

Although the intervention itself is relatively simple, its effects are realised through complex processes, like the behaviour (change) of people with diabetes. The effect of the intervention will partly depend on factors related to the process itself (for instance, the level of interaction and personalisation of messages), but also on the profile of people with diabetes (for instance their attitude towards their diabetes and their familiarity with mobile phones) and on the context [48,49].

The multi-country analysis will aim to understand any differences in the effects of the intervention and the role of the context, for instance the design of the existing DSME programme, knowledge and professional habits of diabetes care providers.

The major limitation of our design with individual randomisation at the level of the patient is that within each participating centre, there will be patients in the DSME-only group and in the DSME+DSMS group. Patients can be in contact with each other and this might cause some contamination between DSME-only and DSME+DSMS patients, resulting in a sub-estimation of effect. The individual targeting of the messages and the central management of the DSMS intervention without interference of the educators should minimise this contamination. Another methodological weakness is the lack of local validation of the scales within the questionnaire, which fell beyond the scope of our study. Pretesting and local fine-tuning will partly address this issue. Since we will use the same questionnaire 3 times along the course of the study, we expect that familiarity with the instruments will grow over time.

The growing numbers of patients with chronic life-long conditions, such as diabetes and hypertension, puts an immense burden on health systems and populations [50]. Scarcity of resources and the lack of quality and continuity of health care result to high expenditure and very poor health outcomes. The intervention tested addresses the problem that the greater part of diabetes management takes place without external support and that many challenges, unforeseen problems and questions most of the time occur at the “in-between moments” of the scheduled contacts with the support system, like health care providers and educators. The project exploits the availability of widely accessible equipment and communication technology to narrow the gap between the support system and people with diabetes. In this way, it addresses the need of people with diabetes to combine their life-long condition with their other needs and roles in life and to contribute to their empowerment [51,52]. It will be interesting to evaluate the impact of this complementary DSMS strategy on the workload of the educators and health provides, an important issue for further scaling up in general services (WHO [53]). The study addresses gaps in knowledge and experience on utilization of mobile phone technology to support people with diabetes in developing countries. Results will provide information to decision-makers regarding conditions of implementation in developing countries and possible expected results.

